#### App functionality during the Intervention Phase

Participants in the diet-only control group will not be able to use the app during the Intervention Phase. For these participants, all app functionality will be blocked. Instead, the app will display the number of days remaining until the end of the waiting period. Eight days before the end of the waiting period, the app will send a notification informing participants that the end of the waiting period is near.

For participants in the immediate intervention group, app functionality in the first week of the Intervention Phase will consist of the EMA module and the Graphical Overview Feedback module, similar to the training and the first EMA-only week. In addition, the Adaptive Feedback module will be active. The Adaptive Feedback module provides participants with feedback if they are at risk for overeating. The feedback message consists of a generic warning and a behavioural advice. Detection of a participant’s ‘risky’ moments is based on the answers provided by the participant on the EMA items. To estimate when the participant is likely to eat something unhealthy in the time-period directly following a completed time-contingent sample, the sample data is compared to a set of allocated pre-existing rules that indicate what combinations of states of variables (e.g. scoring high on desire + being at home + feeling bored + feeling calm) are predictive of unhealthy eating. If there is a match between the time-contingent sample and one of the rules, the participant receives adaptive feedback messages via the Think Slim app.

Lastly, at the last day of week 7, a post-intervention assessment will take place during which participants will fill in self-report questionnaires identical to the baseline assessment. Participants are also instructed to obtain a second measurement of weight during week 8, under identical circumstances as during the first EMA-only week.

#### Phase 4: EMA-only week 2 (week 8)

After the Intervention Phase, all participants (immediate intervention group and diet-only control group) enter a second EMA-only week. This week is identical to the first EMA-only week for all participants.

#### Phase 5: Follow-up (FU) Phase

At the end of the second EMA-only week (week 8), participants in the immediate intervention group will be debriefed about the purpose of the trial. Furthermore, they will receive a monetary reward of €50, in coupons. After that, their FU Phase starts. The FU Phase has a total duration of 12 months. Participants are invited to fill out questionnaires (identical to the baseline and post-intervention assessments) and to obtain independent BMI measurements at two time-points during this period: at 3 and 12 months post intervention. They will receive an additional €20, in coupons, per completed FU measurement.

For the diet-only control group, the procedure after the second EMA-only week (week 8) is different. Participants allocated to this group will now receive the Think Slim intervention (weeks 9–14), followed by a third EMA-only week (week 15) and a debriefing. The content and procedure of the Think Slim intervention received by the diet-only control group is identical to that received by the immediate intervention group, except that information concerning the diet and exercise plan is not included. Furthermore, the third EMA-only week is identical to the other two EMA-only weeks. After that, the 12-month FU Phase starts for this group. The procedure of the FU Phase for the diet-only control group is identical to the procedure of the immediate intervention.

### Measures

Several instruments will be used to assess the effects of the Think Slim intervention on BMI and secondary outcomes. Data are obtained by means of self-report instruments, measures taken by healthcare professionals, and EMA data. Figure 1 depicts when each measure is obtained during the flow of the study.

#### Body mass index

Participants are instructed to obtain multiple measurements of body weight and one measurement of height. These measurements are used to calculate BMI. To ensure objectivity, participants are asked to obtain the measurements via a healthcare professional (e.g. a general practitioner, or a physical therapist), or at the university (Think Slim research staff). Participants are further requested to obtain all measurements under identical circumstances (i.e. the same general practitioner or physical therapist).

#### Patterns of eating behaviour

To gain insight in (changes in) eating patterns, EMA data obtained during the first EMA-only week and second EMA-only week will be investigated.

#### Eating styles

The Dutch Eating Behaviour Questionnaire (DEBQ; [60]) will be used to measure eating styles and consists of 33 items across three subscales: external eating, emotional eating and restraint. Each item of the DEBQ is rated on a five-point Likert scale ranging from 1 (seldom) to 5 (very often). Item scores for the three subscales will first be summed separately to obtain an overall score per subscale. Then, for each subscale, the overall score will be divided by the number of subscale items to obtain the final average score per subscale. A high score on one of the subscales indicates a higher tendency to display the respective eating style. The DEBQ was previously found to be internally consistent overall, *α* = 0.79 [61]. The subscales emotional eating (*α* = 0.89), external eating (*α* = 0.078) and restrained eating (*α* = 0.92) were also found to be internally consistent [62].

#### Eating disorder pathology

The Dutch version of the Revised Eating Disorder Examination Questionnaire (EDE-Q; [55]; Dutch translation) will be used to measure eating disorder pathology. This self-report questionnaire consists of 22 items assessing eating pathology, and 6 items assessing diagnostic behaviours such as use of laxatives and purging. The items are scored across four subscales: restraint, weight concerns, shape concerns, and eating concerns. The eating pathology items of the EDE-Q are each scored on a seven-point Likert scale. The diagnostic behaviour items are scored by participants indicating the number of times in the past 28 days that the behaviour occurred. The test-retest reliability of the English version of the EDE-Q was found to be between *r* = 0.66 and *r* = 0.94 for each of the subscales, whereas the internal consistency of the EDE-Q subscales was found to be good, ranging from *α* = 0.70 to *α* = 0.93 [63].

#### General psychological symptomatology

The Brief Symptom Inventory (BSI; [64]: Dutch translation by [65]) will be used to assess general psychological symptomatology, and consists of 53 items. The BSI has nine subscales assessing different forms of psychological distress. Items of the BSI are scored on Likert scales ranging from 0 (not at all) to 4 (very much so). Scores for each subscale are calculated by averaging scores on the individual items belonging to that subscale. The total score for the BSI is calculated by summing all individual item scores. The BSI subscales were found to have satisfactory internal consistency, ranging from *α* = 0.71 to *α* = 0.88 [66]. In addition, the test-retest reliability is high, with the lowest score reported at *r* = 0.68 [66].

#### Self-esteem

The Self-liking and Self-competence Scale Revised (SLSC-R; [67]: Dutch translation by [68]), will be used to assess self-liking and self-competence as dimensions of self-esteem, and consists of 16 items, 8 for each dimension. Items are rated on five-point Likert scales ranging from 1 (strongly disagree) to 5 (strongly agree). Overall scores per dimension are obtained by summing scores of individual items belonging to each dimension, and can range between 8 and 40. Higher scores indicate more self-competence and self-liking than lower scores. Internal consistency of the subscales of the Dutch translation of the SLSC-R was found to be good, ranging from *α* = 0.78 to *α* = 0.98 [68]. Split-half reliability for the subscales was also found to be good, ranging from *r* = 0.75 to *r* = 0.92.

#### Acceptability and compliance

Acceptability of the Think Slim intervention will be measured using a questionnaire that was developed for the current study. This questionnaire includes items on user-friendliness and perceived usefulness of the Think Slim intervention. Compliance with the EMA module in the app will be measured daily during the study by calculating how many time-contingent samples were completed by participants relative to the total number of time-contingent samples that were sent by the app, and by monitoring how often the Cognition Evaluation module of the app was used.

### Data analysis

Participant’s flow from screening to randomisation will be mapped out. Furthermore, pre-treatment characteristics of the sample will be explored, and baseline differences between conditions will be examined in terms of size and clinical importance. Distributions of outcome variables will be inspected via histograms and boxplots. After that, intervention- and study-compliance will be determined, followed by an evaluation of participants’ satisfaction with the Think Slim intervention.

To test the effectiveness of the Think Slim intervention, 2 (group: immediate intervention versus diet-only control group) × 2 (time: pre versus post) analyses of variance (ANOVAs) will be run for the set of dependent variables (i.e. BMI, dysfunctional thinking, scores for questionnaires on eating styles, eating disorder pathology, general psychological symptomatology, and self-esteem). Long-term effects of the Think Slim intervention on the set of dependent variables will be examined using one-way repeated-measures ANOVAs collapsing over group (i.e. for all 102 participants), with four levels: pre-Think Slim, post-Think Slim, 3-month follow-up and 12-month follow-up. All analyses will be performed according to the intention-to-treat principle [69] and the completers principle. Lastly, time-lagged multilevel network analyses will be conducted on data obtained during the pre- and post-Intervention Phase EMA-only weeks, to assess changes in patterns of data that result in unhealthy eating [31, 37]. Changes in network connectivity between the pre- and post-Intervention Phase networks will be compared between both conditions. Of particular interest are changes in network connectivity and density related to unhealthy eating, in terms of graph analysis measures such as indegree, outdegree, betweenness, and centrality of network nodes.

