### Sample size

Sample size was calculated a priori using G*Power [56]. Prior effect size estimates are not available because the current study will be the first to investigate an EMI for weight loss. Power analysis indicated that with 51 participants in each condition, the study is powered at 80.6 % (two-tailed, *α* = 0.05) to detect a standardised medium effect size difference (Cohen’s *d* = 0.5; [57]) in BMI change between the two conditions. To account for an expected 23.5 % attrition rate (derived from attrition rates in EMI studies with ten or more participants, reported in [29]), the aim is to recruit a total of 134 participants.

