#### Randomisation

After completing the technical training, all participants will be contacted by the researchers to discuss possible issues that occurred during the training. Subsequently, randomisation will take place. Participants will be randomly assigned to either the immediate intervention group or the diet-only control group using computer-generated randomisation via Research Randomizer (www.randomizer.org). More specifically, randomisation is pre-stratified by age group (18–30; 31–40; 41–50; 51–60) and gender. For each age group, separately for male and female participants, each participant will be assigned a randomly generated number. Half of the participants with the largest randomly generated numbers will be assigned to the immediate intervention group, whereas the other half will be assigned to the diet-only control group. Note that participants who indicate as being unavailable during a specific time period, due to for example holidays, will be manually allocated to the condition that matches with their availability. Blinding participants and researchers is not possible in the current setup.

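### The 2 × 2 ANOVA omits the age and gender strata and fixes the baseline slope at 1, which can cost precision but does not inflate type I error

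*Protocol article*

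**What the plan says.** The Randomisation section of the protocol article says that "randomisation is pre-stratified by age group (18–30; 31–40; 41–50; 51–60) and gender". That makes 4 × 2 = 8 strata. Within each stratum the split is equal: "Half of the participants with the largest randomly generated numbers will be assigned to the immediate intervention group", and the rest go to control. There is one exception. Participants who are unavailable in a given period "will be manually allocated to the condition that matches with their availability"; their number is not given.

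The Data analysis section names the effectiveness test for BMI and all questionnaire outcomes as a group (two levels) by time design: "time: pre versus post) analyses of variance (ANOVAs) will be run for the set of dependent variables". No stratification factor and no baseline covariate appears in that model. Baseline is otherwise handled descriptively: "baseline differences between conditions will be examined in terms of size and clinical importance".

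The Sample size section powers the trial on the difference in BMI change, "with 51 participants in each condition", d = 0.5, "two-tailed, *α* = 0.05".

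**The concern.** Equal allocation within age-by-gender strata largely removes between-stratum variation from the sampling error of the group difference. A model without the strata still counts that variation as noise. If age and gender predict change, its confidence intervals are wider than they need to be and its test rejects too seldom.

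Separately, a change-score analysis subtracts the whole baseline value, which amounts to a slope of 1. When pre and post values are only moderately correlated, the best slope is below 1, and estimating it gives a more precise comparison from data that the trial already collects.

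At stake are power and interval width. There is little power to spare: at 51 per arm, two-tailed power for d = 0.5 is about 71%.

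**Working it through.** **Inputs from the protocol:** 51 evaluable per arm, d = 0.5 on BMI change, two-tailed α = 0.05, 23.5% attrition, 134 recruited, 8 strata.

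**Assumed, because the protocol gives neither:**
- R², the share of variance in change explained by the strata: 0 to 20%.
- ρ, the pre–post correlation: 0.90–0.99 for BMI over about 8 weeks, 0.5–0.8 for questionnaires.

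**Step 1. The plan's own figure.** The noncentrality is 0.5 × √(51/2) = 2.525 on 100 degrees of freedom. Two-tailed power is 70.6% (noncentral t), not 80.6%. The stated figure reproduces only as a one-tailed test (80.59%). The attrition step does reproduce: 102/(1 − 0.235) = 133.3, rounded up to 134. The baseline for comparison below is therefore about 71%.

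**Step 2. What the planned test is.** With two time points, the group-by-time F equals the square of the two-sample t on change. On a simulated data set both came to 2.8838.

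**Step 3. Strata left out.** With balanced strata:
- The unadjusted standard error is overstated by the factor 1/√(1 − R²).
- The actual two-sided α is 2 × [1 − Φ(1.96/√(1 − R²))].
- Unadjusted power is Φ[(2.525 − t₀.₉₇₅,₁₀₀)/√(1 − R²)].
- Adjusted power uses an effect of 0.5/√(1 − R²) and 96 degrees of freedom (three for age group and one for gender removed).

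| R² | SE too wide by | Actual α | Power, unadjusted | Power, adjusted |
|---|---|---|---|---|
| 0 | 0% | 0.050 | 70.6% | 70.5% |
| 5% | 2.6% | 0.044 | 71.1% | 72.7% |
| 10% | 5.4% | 0.039 | 71.6% | 75.0% |
| 20% | 11.8% | 0.028 | 72.7% | 79.8% |

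A simulation with 8 strata and 8,000 runs per setting agreed. Unadjusted α was 0.054, 0.047, 0.036 and 0.030 down the rows; adjusted α stayed between 0.048 and 0.054. Fitting all 8 cells instead of the two main effects changed the computed power by less than 0.1 percentage points.

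**Step 4. Slope fixed at 1.** With equal pre and post variance σ², a change score has variance 2σ²(1 − ρ) and the ANCOVA residual has σ²(1 − ρ²). Their ratio is (1 + ρ)/2, so the standard error falls by 1 − √((1 + ρ)/2). Power is for 51 per arm with d = 0.5 on change.

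| ρ | SE reduction | Power |
|---|---|---|
| 0.99 | 0.25% | 70.8% |
| 0.98 | 0.5% | 71.0% |
| 0.95 | 1.3% | 71.6% |
| 0.90 | 2.5% | 72.7% |
| 0.8 | 5.1% | 75.0% |
| 0.7 | 7.8% | 77.4% |
| 0.6 | 10.6% | 79.8% |
| 0.5 | 13.4% | 82.3% |

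The first four rows cover BMI, the last four the questionnaires. The trial is not sized on the questionnaires, so d = 0.5 there is only a common yardstick.

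**The case against.** The planned test is standard and valid, and several points against the concern stand.

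- A reader might infer that the analysis ignores baseline. It does not: the pre value is a level of the time factor and the interaction is an analysis of change, matching the quantity on which the trial is sized. Only the estimated slope is missing.
- A reader might take it as fact that the confidence intervals are too wide. The protocol does not say how well age and gender predict change. If they predict nothing, omitting the strata costs nothing.
- Comparing adjusted power with a fixed 70.6% overstates the gain, because stratified allocation also raises the power of the unadjusted test. At R² of 5 and 10% the gains are about 1.6 and 3.4 points (72.7 − 71.1 and 75.0 − 71.6), not 2.1 and 4.4.
- Manual allocation and the expected 23.5% attrition disturb the balance among those analysed, so the figures in Step 3 are idealised.
- The ratio (1 + ρ)/2 is a large-sample result assuming equal variances. For BMI the gain is so small that estimating the slope offsets part of it.

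One argument does not carry. Covariates are often left to an analysis plan, and none is shown here. But this article does more than stay silent: it names a specific model, and that model does not reflect the stratified randomisation described under Randomisation.

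**Conclusion.** The point holds as a modest efficiency finding. The named model leaves out the randomisation factors and an estimated baseline slope. The two losses differ in kind: omitting strata makes the standard error conservative, while the change score has a valid standard error that is larger than necessary. Neither inflates type I error.

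For BMI the slope matters little, so any material gain would have to come from the strata, and its size rests entirely on the assumed R², which may be zero. For the questionnaires the slope matters more, on the assumed correlations.

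Two further inferences are not supported. Adjustment does not restore the stated 80.6% power for BMI: that figure is the one-tailed value labelled two-tailed, a separate error needing its own correction. Nor does adjusting for age and gender remove the risk of bias from manual allocation, since availability may relate to outcome in ways that these factors do not capture.

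**What to change.** In Data analysis, make the effectiveness test an ANCOVA of each post-intervention outcome on group, its baseline value, age group and gender, or an equivalent baseline-constrained mixed model. Apply it to BMI and to each questionnaire score. Report the adjusted mean difference with its 95% confidence interval, and keep the 2 × 2 ANOVA as a supporting analysis.

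The cost is a change of wording and about 5 degrees of freedom: one for baseline, three for age group, one for gender. All the covariates are already collected, and the article gives the trial status as recruiting.

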### Aims and hypotheses

The current study aims to test the effectiveness of the Think Slim intervention. In a randomised controlled trial, overweight participants will actively follow a diet of their own choice. In addition, they will be instructed to exercise according to their own personal exercise plan. Half of the participants will receive the Think Slim intervention immediately (immediate intervention group). The other half will start with a diet only (diet-only control group). Participants in this latter group will receive the Think Slim intervention afterwards. Whether diet + Think Slim is superior to diet only in the reduction of BMI will be examined together with a set of secondary post-intervention outcomes. Secondary outcomes include (1) self-report questionnaires of dysfunctional thinking, eating styles, general psychological distress, eating disorder pathology, and self-esteem, and (2) network patterns that lead to unhealthy eating. It is expected that over the course of receiving the Think Slim intervention, participants in the immediate intervention group will experience (1) greater reduction in BMI, (2) greater improvements on dysfunctional thinking, self-report questionnaires of eating styles, eating disorder pathology, general psychological symptomatology, and self-esteem, and (3) have less dense network connectivity related to unhealthy eating, as compared to participants in the diet-only control group. Lastly, it is expected that, for both groups taken together, reductions in BMI and improvements in secondary measures will have been maintained at the 3- and 12-month follow-up measurements.

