#### Phase 3: Intervention Phase (weeks 2–7)

After the first EMA-only week, the Intervention Phase starts. This phase has a total duration of 6 weeks (weeks 2–7).

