#### Diet

During the Intervention Phase, all participants (immediate intervention group and diet-only control group) are asked to actively follow a calorie-restrictive diet of their own choice. Supervision of the diet by a dietician or healthcare professional is not allowed. Instead, all participants select a diet coach (friend or family member). Participants will also develop an exercise plan. General information about dieting and exercising is provided as part of two online sessions in the first week of the Intervention Phase. At the end of the first week, participants are asked to finalise their choice. Aside of the two online sessions, no further information about selecting a diet is provided.

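### The pooled long-term ANOVA uses a pre-Think Slim level that precedes the diet phase in one arm and follows it in the other, so early diet loss enters a result labelled as a Think Slim effect

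*Protocol article*

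**What the plan says.** Data analysis sets out the long-term analysis as follows: "Long-term effects of the Think Slim intervention on the set of dependent variables will be examined using one-way repeated-measures ANOVAs collapsing over group". It covers all 102 participants and has four levels: before Think Slim, after Think Slim, and the 3- and 12-month follow-ups. It has no group factor. The matching hypothesis, under Aims and hypotheses, is that "for both groups taken together, reductions in BMI and improvements in secondary measures will have been maintained at the 3- and 12-month follow-up measurements".

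The schedule is given elsewhere in Methods:

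- **Diet.** In the Intervention Phase (6 weeks, weeks 2–7), "all participants (immediate intervention group and diet-only control group) are asked to actively follow a calorie-restrictive diet of their own choice".
- **Immediate arm.** It receives Think Slim in those same weeks. Its baseline questionnaires and BMI are taken in week 1 (Phase 2).
- **Control arm.** It receives Think Slim in weeks 9–14 (Phase 5), with the same content "except that information concerning the diet and exercise plan is not included". Its last measurements before that are the questionnaires on the last day of week 7 and the weight in week 8.
- **Follow-up clock.** The note to Fig. 1 counts 3 and 12 months from the end of each arm's own last EMA-only week.

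**The concern.** One label, pre-Think Slim, covers two different states. In the immediate arm it means not yet in the diet phase. In the control arm it means after the diet phase. Pre-to-post change is thus diet plus Think Slim in the first arm. In the second it is Think Slim plus whatever the diet still yields in weeks 9–14. A model without a group term averages the two and presents the result as the long-term effect of Think Slim. By then every participant is scheduled to have had Think Slim, so no concurrent comparison can separate diet from intervention.

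Long-term weight loss is the rationale given in the Background and Discussion, and this is the only analysis that the article sets out for it. Followed as written, it can credit ordinary early diet loss to Think Slim.

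**Working it through.** **Plan's own figure.** The article gives no effect size or power for this analysis, only its N. That N is the sample-size target: 2 × 51 = 102. The check below uses 51 per arm.

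**Position of the four levels**

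| Level | Immediate arm | Control arm |
|---|---|---|
| Pre | week 1, before the diet phase | week 7/8, after the diet phase |
| Post | week 7/8 | after weeks 9–14 |
| 3 and 12 months | from end of week 8 | from end of week 15 |

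The control arm's pre level is inferred from the phases, because Fig. 1 is not shown. The stated phases leave no pre-diet alternative.

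**Expected pre-to-post loss.** Let D be the loss over the diet phase, T the loss added by Think Slim, and D2 any further diet loss of the control arm in weeks 9–14.

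- Immediate arm: D + T
- Control arm: T + D2
- Pooled, equal arms: (D + T + T + D2)/2 = T + D/2 + D2/2

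Half of D always enters. The diet share of the pooled loss is (D/2 + D2/2)/(T + D/2 + D2/2).

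**Size.** The article gives no D, T or D2, so the values below are assumptions, in units of the SD of change between two visits.

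| D | T | D2 | Immediate | Control | Pooled | Diet share of pooled |
|---|---|---|---|---|---|---|
| 0.5 | 0.5 | 0 | 1.0 | 0.5 | 0.75 | 0.25/0.75 = 33% |
| 0.5 | 0.25 | 0 | 0.75 | 0.25 | 0.50 | 0.25/0.50 = 50% |
| 0.8 | 0.2 | 0 | 1.0 | 0.2 | 0.60 | 0.40/0.60 = 67% |
| 0.5 | 0 | 0 | 0.5 | 0 | 0.25 | 0.25/0.25 = 100% |
| 0.5 | 0.5 | 0.25 | 1.0 | 0.75 | 0.875 | 0.375/0.875 = 43% |

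Comparing the first and last rows, continued dieting in the control arm raises the diet share.

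**When Think Slim adds nothing (T = 0, D2 = 0).** The four-level ANOVA was simulated on 2 × 51 participants, with 3,000 runs per setting, a 0.05 level, and independent visit errors of SD 1/√2 (so a change between two visits has SD 1). The entries are the share of trials with a significant time effect.

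| D | All loss kept | Half of total loss regained by 12 months |
|---|---|---|
| 0 | 4% | 5% |
| 0.25 | 23% | 20% |
| 0.5 | 73% | 66% |
| 0.8 | 99% | 98% |

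With D = 0 the rate is near the nominal 5%, so the excess comes from the diet phase alone.

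**Retention measured against the pre level.** Take D = T = 0.5 and D2 = 0, and let each arm regain half of its total loss since week 1 by 12 months. The one-half follows the average that the Background reports for earlier programmes and is not a forecast for this trial.

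- Immediate arm: 0.5 of 1.0 kept, 50%.
- Control arm: it ends 0.5 below week 1, which is exactly its pre level, so 0 of 0.5 is kept, 0%.
- Pooled: (0.5 + 0)/(1.0 + 0.5) = 33%.

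With D2 = 0.25 the three figures are 50%, 17% and 36%. Measured from week 1, both arms keep 50% in either case. The post-to-12-month regain is 0.5 in each arm when D2 = 0, and 0.5 against 0.625 when D2 = 0.25.

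**The case against.** The strongest reply has four parts.

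1. **Maintenance concerns what happens after treatment.** The natural contrasts are post to 3 months and post to 12 months. They do not touch the pre level, and both arms are timed from their own last EMA-only week. This stands. A reader might infer that the pooled analysis says nothing valid about maintenance in either arm, but the article does not support that: the defect lies in the overall time effect and in contrasts against pre. A post-to-follow-up average still mixes arms at different distances from the start of the diet (15 − 8 = 7 weeks apart), which is a reason to report by arm.

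2. **The article does not say how maintenance will be decided.** A reader might infer that it will be declared from the omnibus F, or from a non-significant post-to-12-month difference. Neither rule is stated, and follow-up contrasts are commonly left to an analysis plan.

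3. **The control arm is not told to stop dieting.** Only information on diet and exercise is left out of its later sessions, and Table 1 (note a) shows that both arms had already completed that component. Reading the control arm's change as Think Slim alone is therefore too clean, and so is any claim that this arm must end above its pre level, which requires no further diet loss. This stands. It weakens attribution to Think Slim further, because D2 adds to the pooled figure.

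4. **Pooling and the loss of a control are disclosed features of a delayed-intervention design.** The hypothesis openly takes both groups together, and no re-analysis restores a control. This is true, but disclosure does not align the two pre levels or justify the label given to the result.

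**Conclusion.** The point holds for the overall time effect and for every contrast against pre-Think Slim. The pooled pre-to-post loss is about T + D/2, plus D2/2, so a time effect can appear when Think Slim adds nothing. For assumed diet-phase losses of 0.25 to 0.8 SD, it appeared in 23% to 99% of simulated trials with all loss kept. The algebra depends only on the schedule and equal arm sizes. The percentages depend on the assumed effect sizes, on independent errors and on no further diet loss in the control arm. Participants finalise their diet at the end of the first intervention week, so time on the final diet before week 8 may be nearer 5 weeks than 6. That affects the size of D, not the argument.

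A reader might extend this to the effectiveness test. The article does not support that: the 2 × 2 pre/post comparison uses the randomised arms over the same weeks, with both asked to diet, and is unaffected. This is a should-fix for the secondary long-term analysis.

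**What to change.** In Data analysis:

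- Replace the pooled one-way ANOVA with a group × time model (a mixed model with group retained).
- Report each arm's change from its week-1 pre-diet baseline as well as from its own pre-Think Slim point, and say which visit that point is in each arm.
- Base the maintenance statement on the post-to-3-month and post-to-12-month changes, by arm, with confidence intervals. If a limit for acceptable regain is used, state it beforehand. The 50% average in the Background should not serve, because it is presented there as the shortcoming of existing treatment.
- Describe these results as uncontrolled within-person change after diet plus Think Slim, and reword the sentence that calls them effects of Think Slim.

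The planned visits already supply the data, so the cost is analysis work and wording. Estimates by arm are somewhat less precise than a pooled one, and the long-term claim becomes more modest.

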## Methods

### Trial design

A randomised controlled superiority trial will be conducted, in which 134 overweight (BMI above 25 kg/m^2^) participants will follow a diet of their own choice. In addition, they will exercise according to their own personal exercise plan. Participants are split into two groups. The two groups will run in parallel. The immediate intervention group (*n* = 67) will immediately receive the Think Slim intervention in addition to their chosen diet. During this time, the diet-only control condition group (*n* = 67) will receive no further support. The diet-only control condition group will receive the Think Slim intervention after the immediate intervention group has completed the intervention. The enrolment procedure is graphically shown in Fig. 1. The trial has been approved by the Ethics Committee of the Faculty of Psychology and Neuroscience of Maastricht University (The Netherlands), and is registered at the Dutch Trial Register, part of the Dutch Cochrane Centre (NTR5473). The study will adhere to recommendations of the Consolidated Standards of Reporting Trials (CONSORT) [54].

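### The long-term ANOVA is fixed on 102 participants, the expected post-attrition number, while all analyses are said to follow intention-to-treat, for which the target is 134

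*Protocol article*

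**What the plan says.** The Sample size section of the protocol article bases power on a BMI comparison "with 51 participants in each condition". It then allows for loss: "To account for an expected 23.5 % attrition rate", "the aim is to recruit a total of 134 participants". Trial design gives 67 per group.

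The Data analysis section names two kinds of ANOVA:

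- A 2 x 2 group-by-time ANOVA (pre versus post) tests effectiveness on BMI and the questionnaire outcomes. No N is attached to it.
- A one-way repeated-measures ANOVA with four levels (before and after Think Slim, 3 months, 12 months) examines long-term effects. It is described as "collapsing over group (i.e. for all 102 participants".

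The next sentence begins "All analyses will be performed according to the intention-to-treat principle" and goes on to add the completers principle. It does not say which of the two is primary.

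The section on the cognitive intervention, headed as applying to the immediate intervention group only, defines dropouts by online sessions: not finishing all five in the first intervention week, or later having more than one overdue.

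**The concern.** Intention-to-treat means everyone randomised, analysed as allocated. If the long-term analysis is run on the number expected to survive attrition, it is not intention-to-treat, whatever the next sentence says. People who leave a weight-loss programme may well have done worse than those who stay. A maintenance result based only on those who stay could then look better than the result for everyone who started.

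Two further features make the ambiguity matter:

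- The named method needs all four measurements from each person. Without imputation, a participant who misses only the 12-month visit loses the other three measurements too.
- Completer status in the intervention arm depends on adherence to the sessions. During the randomised comparison the diet-only group has only two online sessions on diet and exercise, and the article states no dropout rule for it. A completers comparison could then remove poor adherers from one arm only, which favours the intervention if poor adherers lose less weight. With both sets on equal terms, nothing in the article says which result stands if they disagree.

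**Working it through.** **Inputs.** From Sample size: 51 per condition, 23.5 % attrition, 134 to be recruited. From Trial design: 67 per group. From Data analysis: 102 participants in the long-term ANOVA.

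**Step 1: reproduce the plan's recruitment figure.** Recruited = evaluable / (1 - attrition).

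- Per arm: 51 / (1 - 0.235) = 51 / 0.765 = 66.7, rounded up to 67.
- Total: 102 / 0.765 = 133.3, rounded up to 134.

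Both match the document.

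**Step 2: identify the 102.** 2 x 51 = 102. In reverse, 134 x 0.765 = 102.5, or about 102. The article offers no other source for this number, so it is the expected post-attrition count.

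**Step 3: size of the conflict.** 134 - 102 = 32, and 32 / 134 = 23.9 %. The gap between the stated N and the intention-to-treat target is the attrition allowance.

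**Step 4: where the 102 applies.** It is attached to the one-way, four-level ANOVA collapsed over group. It is not attached to the 2 x 2 ANOVA that makes the randomised comparison.

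**Step 5: do the two analysis sets differ?** The session rule defines dropout by unfinished sessions. Weight is obtained separately, from a healthcare professional or at the university (section on body mass index). A session dropout who is still weighed belongs in the intention-to-treat set and outside the completers set. The two sets can therefore differ in the pre-post comparison even under plain ANOVA. The article does not say how many dropouts would still be weighed.

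**The case against.** The strongest reply has four parts.

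- *Both principles are announced.* The 102 could be the expected N of the completers version, or a leftover from the power calculation. That is possible, but the text ties it to neither and calls these all the participants, so the statement still needs correcting.
- *The long-term analysis is secondary and has no randomised comparison.* This stands, and it limits the reach of the N error. A reader might infer that 32 people are excluded by design from the primary comparison. The document does not support that: the 2 x 2 ANOVA carries no N, and 23.5 % is an expected attrition rate, not an exclusion rule.
- *Complete-case analysis is never stated.* This also stands. Listwise deletion is what a classical repeated-measures ANOVA does by default, but imputation is not ruled out, and an article may leave the missing-data method to the full protocol or analysis plan. A reader might conclude that the stated intention-to-treat analysis is really a completers analysis; that goes beyond the text, and Step 5 shows the two sets can differ.
- *A mixed model is one choice among several.* Agreed. ANOVA on multiply imputed data would also serve.

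**Conclusion.** The point holds in a limited form. The N stated for the long-term ANOVA contradicts the intention-to-treat statement that follows it, by 32 of 134 (23.9 %). This rests only on the document's own figures, which reproduce. The equal standing of the two analysis sets is a real weakness for BMI, because completer status depends on session adherence in one arm, with no matching rule stated for the other during the randomised comparison. The direction of any bias is an assumption: it favours the intervention if poor adherers lose less weight. The loss of partial data applies to a classical four-level ANOVA without imputation.

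The correction should not be presented as a gain in power. At d = 0.5, two-tailed, power is 70.6 % with 51 per arm and 81.9 % with 67 per arm, and a reader might infer that the change moves the trial from one to the other. It does not. The higher figure needs a post-intervention weight from all 67 per arm and an undiluted effect. A mixed model cannot supply missing weights, and a participant with only a baseline value adds little to a two-time-point comparison. That the printed 80.6 % is reproduced one-tailed but not two-tailed is a separate matter.

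**What to change.** 1. In Data analysis, replace 102 with all randomised participants (target 134) for the intention-to-treat analysis, and give about 102 as the expected number of completers.
2. Name intention-to-treat, as allocated, as the primary analysis of BMI and the completers analysis as secondary.
3. Analyse the repeated measures with a linear mixed model that uses every available measurement, so that a missed visit does not remove a person's other data. ANOVA on multiply imputed data is an acceptable alternative.

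The cost is wording and modest programming, with no change to data collection. The article gives the trial status as recruiting, so the choice can be fixed before results could influence it.
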